#### Strategies to improve adherence to interventions {11c}

A record of the children’s attendance and percentage of participation in each session (for both groups) will be made. In addition, a research team member will register each session’s incidents and observations. For example, there will be a registry of the number of children playing every 5 min, and the reasons why the children are not performing the task will also be noted (e.g. going to the bathroom, a problem with the tablet, etc.). Finally, once every 15 days, a meeting will be held with all the educators to evaluate the possible doubts and difficulties in developing the programme.

#### Relevant concomitant care permitted or prohibited during the trial {11d}

The schools participating in the study cannot implement other programmes stimulating cognitive and socio-emotional skills during the trial.

#### Provisions for post-trial care {30}

There is no harm nor potential harm in this trial. The intervention group will receive an intervention built under the best evidence available to stimulate preschoolers’ cognitive, social, and emotional skills. The active control group will receive a tablet game programme where they will only paint. We have included several benefits for children and schools participating in the study: (1) A report with the data collected will be provided to all schools (without the children’s identity) to help the institutions plan future measures to be included in the regular teaching activities to stimulate development. (2) Additionally, those parents or main caregivers who request information about the results of the measures carried out on their children will be granted. (3) We have offered to all schools some training opportunities for early educators to gain new skills related to promoting cognitive and non-cognitive skills among children. This training will be implemented after the final follow-up assessment.

### Outcomes {12}

#### Primary outcomes

Tests of academic skills:1.1.Initial literacy learning: Two tests will be used: Texas Lee, designed by the Texas Education Agency [27] in collaboration with the University of Houston to evaluate reading in Spanish-speaking children. This instrument has been validated for Chile by Medina et al. [28]. It considers the following dimensions: Knowledge of the printed, Knowledge of the alphabet, Phonological/phonemic awareness, and Oral comprehension (*a* =.82). To evaluate vocabulary, the Spanish adaptation of the Kaufman Assessment Battery for Children (K-ABC) [29] will be used, and it was also validated for this age group by Medina et al. [28] (*a* =.79). Each correct answer will be registered as one point. The total score means the number of correct answers. We will assess the difference between groups at each point in time (immediately after stimulation, at 6, 12, 18, and 24 months), using the mean score of the group, adjusting by baseline mean scores.1.2.Pre-calculation skills: Woodcock-Muñoz (Battery III [30]), includes the following subtests of the achievement test: Quantification, Verbal Counting, Identification of numbers, and Applied Problems. Split-half reliability for Spanish-speaking children ages 4 and 5 ranges from .93 to .95. Each correct answer will be registered as one point. The total score means the number of correct answers. We will assess the difference between groups at each point in time (immediately after stimulation, at 6, 12, 18, and 24 months), using the mean score of the group, adjusting by baseline mean scores.

#### Secondary outcomes

2.Mental health problems: Goodman’s “Strengths and Difficulties Questionnaire” (SDQ) [31] will be utilized. It consists of a series of emotional and behavioural problems experienced by children between 4 and 16 years old. It has four subscales of psychological difficulties (of 5 items each): emotional symptoms, behavioural problems, hyperactivity/attention problems, peer problems, and prosocial behaviour. These subscales can be combined into a Difficulties subscale with a total score. The version for children and young people in Chile was validated by the team of this project [name] et al. [32], with an internal consistency through the McDonald’s Omega index, which fluctuates between .76 and .85 (report from main caregivers). We will assess the difference between groups at each point in time (immediately after stimulation, at 6, 12, 18, and 24 months), using the mean score of the group, adjusting by baseline mean scores.3.Cognitive Skills Tests:3.1.Working memory: 2 memory tests will be applied: visual-spatial and phonological. For the visuospatial area, the “Corsi Cube test” [33] will be administered. It involves repeating a sequence of up to nine spatially separated identical blocks on a screen. The series starts simple but becomes more complex until the subject’s performance decreases (internal consistency between .75 and .78. For the phonological area, the auditive memory subtest of Woodcock-Muñoz (Battery III [30]) (internal consistency .80) will be used. A sequence of audio messages is presented from lowest to greatest difficulty, and the child is asked to remember these messages. Each correct answer will be registered as one point. The total score means the number of correct answers. We will assess the difference between groups at each point in time (immediately after stimulation, at 6, 12, 18, and 24 months), using the mean score of the group, adjusting by baseline mean scores.3.2.Inhibitory control: the “Hearts & Flowers” task [34] will be used, which is a hybrid that combines elements of Simon and spatial tasks of Stroop and contains congruent and incongruous essays. For congruent trials, subjects must obey the rule: “Press on the same side as the stimulus (Hearts)”. For incongruous trials, subjects should follow the rule: “Press on the side opposite the stimulus (Flowers)”. The test showed a Cronbach alpha of .83. Each correct answer will be registered as one point. The total score means the number of correct answers. We will assess the difference between groups at each point in time (immediately after stimulation, at 6, 12, 18, and 24 months), using the mean score of the group, adjusting by baseline mean scores.4.Socio-emotional Skills Tests:4.1.Emotion recognition: the “Assessment of Children’s Emotional Skills” (ACES) by Schultz et al. [35] will be administered. The test comprises three subscales: facial expressions, social situations, and social behaviour. The current project will administer the subscale of facial expressions (*a* =.68). Each child will need to identify correctly 16 facial expressions. Each correct answer will be registered as one point. The total score means the number of correct answers. We will assess the difference between groups at each point in time (immediately after stimulation, at 6, 12, 18, and 24 months), using the mean score of the group, adjusting by baseline mean scores.4.2.Selection of prosocial behaviours: the “Challenging Situations Task” (CST) by Denham et al. [36] will be employed, reporting a Cronbach alpha of .83. The instrument assesses children’s ability to solve problems. Children are presented with peer problems, and their responses are classified into four possibilities: prosocial, aggressive, crying, and avoidant. Each option selected by children will be summed in a subsequent subscale. The prosocial subscale will be used as the main comparator between groups. We will assess the difference between groups at each point in time (immediately after stimulation, at 6, 12, 18, and 24 months), using the mean score of the group, adjusting by baseline mean scores.

### Participant timeline {13}

Table 1 shows the participant’s timeline.

**Table 1 Tab1:**
[figure not shown]
Standard Protocol Items: Recommendations for Interventional Trials (SPIRIT) diagram

### Sample size {14}

To determine a significant difference (alpha =0.05) in the measure of the primary outcome (academic skills: early literacy/precalculus), between the comparison and intervention groups, with a power of 80%, we need to recruit six schools with a total of 264 students per group, with an average of 44 students per school (distributed in two courses). For the sample calculation, the Stata statistical package was used, and the “clustersampsi” command, which indicates the differences between groups concerning an average score and considers the correlation effect between the subjects within the same school through the intracluster correlation coefficient (ICC = 0.02) [11]. The information to feed this equation was extracted from a previous study [37], where the control group in the early literacy variable post-intervention measure had a score of 20.06 (DS = 8.32). Assuming a difference in favour of the intervention group of 0.4 DS, the sample size was calculated for this study. In addition, it is estimated that 10% of eligible students might not want to participate, and estimating a 20% loss in follow-up, each group should initially recruit 377 students. This implies that four extra schools will be recruited per group, totalling 16.

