## Statistical methods

### Statistical methods for primary and secondary outcomes {20a}

First, descriptive analyses will be performed to evaluate the balance of variables between groups at the beginning of the study. The primary analysis will be conducted based on intention-to-treat. This analysis includes all randomized subjects in the groups, regardless of whether or not they complete the treatment or follow-up period. Multivariate regression models of mixed effects will be carried out considering as a dependent variable the performance in the tests of academic skills (initial literacy and precalculus) and as an independent variable belonging to the intervention or comparison group, controlling for gender, age (in months), mental health, and performance in the same tests in the baseline evaluation. Regression models will consider the nested nature of the data (clustering), since students’ performance within the same educational establishment tends to be correlated. While primary outcomes will be considered as those obtained after the intervention, analyses will be repeated for follow-up at 6, 12, 18, and 24 months. This will allow for evaluation of the maintenance of the effect of the intervention until first grade. We will use mixed-effect regression models of repeated measures to assess convergence and divergence between groups in follow-up times. Subgroup analyses will be performed for the primary outcome variable using interaction terms in the regression models between the randomized groups and the gender variable. This will allow us to evaluate the moderating effect. Sensitivity analyses will also be performed to assess the impact of lost data using multiple imputations. The results with and without imputed data will be presented and compared. The tests will be done with Stata 15.0.

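### One alpha of 0.05 is set for two primary domains with no success rule; if either domain suffices, the false-positive rate is about 7% to 10%

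*Protocol article*

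**What the plan says.** Sample size {14} states its aim as "To determine a significant difference (alpha =0.05) in the measure of the primary outcome (academic skills: early literacy/precalculus"), one outcome with a slash between two domains. It concludes that "with a power of 80%, we need to recruit six schools with a total of 264 students per group". The cluster size behind this is 44 students in each school, and the calculation allows for clustering "through the intracluster correlation coefficient (ICC = 0.02"). The only outcome data used are for early literacy: the control group of an earlier study "had a score of 20.06 (DS = 8.32"), with an assumed difference of 0.4 SD.

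Outcomes {12}, under the primary outcomes, has two numbered entries, literacy (1.1) and pre-calculation (1.2). For literacy it says "Initial literacy learning: Two tests will be used", naming Texas Lee and K-ABC vocabulary. It does not say whether they form one score. Both entries end with the same plan: "We will assess the difference between groups at each point in time", followed by five post-intervention times.

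Statistical methods {20a} narrows the time point: "While primary outcomes will be considered as those obtained after the intervention", with the 6 to 24 month analyses as repeats. It names both domains as dependent variables in the main models. The mediation models later in that section are fitted separately for the two domains. No section splits or orders alpha, or says whether success requires one domain or both.

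**The concern.** The sample size section describes one test at 0.05, while the outcomes and analysis sections describe at least two. Which variables are primary, and whether one or both must succeed, decides what the 0.05 refers to. With that left open, a significant result in one domain and a null result in the other could be reported as showing that the game improves academic skills, and the error rate of that conclusion would exceed the stated 5%. A later rule in an analysis plan could control the error, but it would not reconcile the single-outcome wording of the sample size section with the two entries in the outcomes section.

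**Working it through.** **Inputs from the protocol article.** Alpha 0.05 (taken as two-sided; the article does not say), power 80%, SD 8.32, difference 0.4 SD, ICC 0.02, 44 students per school, six schools and 264 students per group (Sample size {14}); 10% refusal and 20% loss (same section); 18 schools (Abstract) or 16 schools (Sample size {14}). **Assumed:** the correlation between test statistics, which the article does not give.

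**1. Reproduce the plan's figure.**
- Difference: 0.4 × 8.32 = 3.33 points.
- Per group without clustering: 2 × (1.96 + 0.84)² / 0.4² = 98.1, rounded up to 99.
- Design effect: 1 + (44 − 1) × 0.02 = 1.86.
- Normal approximation: 99 × 1.86 = 184 per group, and 184 / 44 = 4.2 schools.
- Whole schools of 44, t test on 2k − 2 degrees of freedom: power is 76.9% with five schools per group and 85.8% with six. Six is the first count above 80%, and 6 × 44 = 264.
- Recruitment: 264 / 0.70 = 377 per group, as stated.

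So the stated size reproduces, as a calculation for a single test at 0.05.

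**2. Error rate if either domain suffices.** For two independent tests: 1 − 0.95² = 9.75%. For correlated normal statistics, the rate is 1 − P(both |Z| < 1.96).

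| Correlation (assumed) | Two tests, two-sided | Two tests, false benefit only |
|---|---|---|
| 0 | 9.8% | 4.9% |
| 0.5 | 9.1% | 4.5% |
| 0.7 | 8.3% | 4.2% |
| 0.9 | 7.0% | 3.5% |

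The last column uses 2.5% per test; at zero correlation it is 1 − 0.975² = 4.9%.

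**3. If Texas Lee and K-ABC vocabulary were tested separately.** Three independent tests give 1 − 0.95³ = 14.3%. The rate is 12.5% at a correlation of 0.5, 10.9% at 0.7 and 8.4% at 0.9. For false benefit alone with independence, it is 1 − 0.975³ = 7.3%.

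**4. Cost of halving alpha.** Power for 0.4 SD at ICC 0.02, t test on 2k − 2 degrees of freedom for k schools per group. The 30.8 analysed per school is 44 × 0.70; the 33 is 264 / 8.

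| Schools per group × analysed per school | Alpha 0.05 | Alpha 0.025 |
|---|---|---|
| 9 × 30.8 (18 schools) | 93.8% | 88.2% |
| 8 × 33 (16 schools) | 91.5% | 84.5% |
| 8 × 30.8 (16 schools) | 90.4% | 82.9% |
| 6 × 44 (stated minimum) | 85.8% | 75.6% |

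Work for one row, 9 × 30.8: design effect 1 + 29.8 × 0.02 = 1.596; effective size 277.2 / 1.596 = 173.7 per group; noncentrality 0.4 × √(173.7 / 2) = 3.73 on 16 degrees of freedom.

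The calculation is in SD units, so it carries over to pre-calculation only if 0.4 SD and ICC 0.02 also hold there. The article gives no separate figures for that domain.

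**The case against.** The strongest reply is that this is a condensed article, that a multiplicity rule is often placed in an analysis plan, and that the 0.05 is only an input to a sample size formula which reproduces. The objectives and hypotheses also join literacy and precalculus with an and. Read as a joint requirement, that brings no inflation. Read as two separately reported hypotheses, 0.05 for each is a defensible convention. This stands as far as the size of the error goes: the inflation depends on an either-domain rule that the article neither states nor excludes. It does not remove the mismatch between one primary outcome in the sample size section and two in the outcomes section.

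Three stronger readings are tempting and not supported.
- A reader might infer three separately tested instruments and an error rate of 14%. The article names two literacy tests but does not say that each is tested on its own; its only explicit separation of models is by domain. The 14% is an upper bound under one open reading, and also needs independence.
- A reader might count two domains at five times, ten tests, for 1 − 0.95¹⁰ = 40%. The statistical methods section makes the post-intervention measurement primary, so the later visits add no primary tests.
- A reader might take 10% as the chance of wrongly declaring the game beneficial. That rate covers false positives in either direction; about half favour the game.

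**Conclusion.** The point holds in limited form. One alpha and one single-test sample size are set against two primary domains, with no rule for success. If either domain can support the effectiveness claim, the two-sided false-positive rate is about 7% to 10% instead of 5%, and the rate of false claims of benefit is about 3.5% to 4.9% instead of 2.5%. These ranges assume two tests at two-sided 0.05 with a correlation between 0 and 0.9. If both domains must be significant, the rate does not exceed 5%. Whether literacy is one score or two is a second open point, and it should be closed at the same time.

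**What to change.** In the outcomes section, define one literacy score (saying how the two instruments are combined, or which one is primary) and one pre-calculation score, both immediately after the intervention. Label the 6 to 24 month comparisons there as secondary, to agree with the statistical methods section. Which literacy score to use is the investigators' choice; the article gives no basis for preferring one instrument.

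Then state one success rule and use it in both the sample size and the statistical methods sections:
- **Either domain suffices:** test the two with Holm at overall 0.05. The smaller p-value is compared with 0.025 and, if that is significant, the other with 0.05. Power per outcome is no lower than the alpha 0.025 column above: about 88% with 18 schools and 83% to 85% with 16, but about 76% with only six schools of 44 per group.
- **Both required:** keep 0.05 for each. The cost is joint power. If 0.4 SD holds in both domains, it is at least 1 − 2 × (1 − 0.938) = 87.6% with 18 schools and at least 1 − 2 × (1 − 0.904) = 80.8% with 16.

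Either route is a change of text and needs no new data. It should be fixed before the outcome data are analysed.

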**Methods:**

A cluster-randomized controlled trial design will be used. A tablet-based video game that stimulates cognitive and socio-emotional skills to improve the development of academic skills is compared with a tablet-based game where students draw and paint with no explicit stimulation of cognitive and socio-emotional skills. Eighteen schools and 750 Chilean preschool students will be recruited. The effectiveness of the intervention will be assessed using a direct evaluation of children on literacy learning and pre-calculation skills at baseline, immediately after stimulation, and at 6, 12, 18, and 24 months post-intervention. The mediating effect of working memory, inhibitory control, emotion recognition, and prosocial behaviours will be assessed on the effectiveness of the intervention.

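### The number of schools to be randomised is given inconsistently: 16 stated, 20 implied by the same sentence, 18 in the abstract; the plan's own student target points to 18

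*Protocol article*

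**What the plan says.** Protocol article, Sample size {14}: the requirement before inflation is "we need to recruit six schools with a total of 264 students per group". Schools are taken to contribute 44 students each on average, from two classes. The inputs are alpha 0.05, 80% power, a difference of 0.4 SD and an "intracluster correlation coefficient (ICC = 0.02"). The section then allows for 10% of eligible students declining and 20% loss to follow-up, and says "each group should initially recruit 377 students". The conversion to schools follows at once: "This implies that four extra schools will be recruited per group, totalling 16".

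Protocol article, Abstract, Methods: "Eighteen schools and 750 Chilean preschool students will be recruited".

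Protocol article, Sequence generation {16a}: the school is the unit of randomisation and allocation is 1:1, so a total of 16, 18 or 20 means 8, 9 or 10 schools per group.

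**The concern.** The sentence that sets the number of schools disagrees with itself and with the abstract. In a cluster trial the number of randomised units is a basic design quantity: it largely determines precision, fixes the degrees of freedom for the comparison, and is the target against which recruitment is judged. A team following the sample size section could stop at 16 schools, and a team following the abstract at 18. A later reader could not tell whether a given number of enrolled schools is under, on or over target. Nothing in the article's text reconciles the three figures. The flowchart (Fig. 1) was not available for this check.

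**Working it through.** **Inputs** (all from Sample size {14} unless noted): alpha 0.05 (two-sided assumed, as sidedness is not stated); power 80%; difference 0.4 SD; ICC 0.02; 44 students per school on average; 10% refusal; 20% loss; 264 and 377 students per group. The abstract gives 18 schools and 750 students.

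**1. The base size reproduces.** Design effect = 1 + (44 - 1) x 0.02 = 1.86. Power for k schools per group uses SE = sqrt(2 x 1.86/(44k)) in SD units and a noncentral t with 2(k - 1) degrees of freedom.
- k = 5: power 76.9%.
- k = 6: SE = sqrt(3.72/264) = 0.1187, 0.4/0.1187 = 3.37, power 85.8%.

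Six is the smallest whole number of schools per group that reaches 80%, and 6 x 44 = 264.

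**2. The inflated target reproduces.** 264/(1 - 0.10 - 0.20) = 264/0.70 = 377.1, so 377 per group and 754 in all.

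**3. The number of schools does not reproduce.**
- Literal reading of the sentence: 2 x (6 + 4) = 20.
- Stated total: 16, that is 8 per group, or two extra per group.
- From the target: 377/44 = 8.57, so 9 per group, 18 in total, or three extra per group.

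The last agrees with the abstract: 18 schools, and 750 students against 754.

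**4. What each count holds.** The retained columns take 44 as eligible children before refusal, and apply the losses additively (x 0.70) or in sequence (0.9 x 0.8 = x 0.72).

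| Schools in total | Places per group | Against 377 | Retained, x 0.70 | Retained, x 0.72 |
|---|---|---|---|---|
| 16 | 8 x 44 = 352 | 25 short | 246 | 253 |
| 18 | 9 x 44 = 396 | met | 277 | 285 |
| 20 | 10 x 44 = 440 | met | 308 | 317 |

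With 16 schools the analysed number is 11 to 18 children per group below 264. To hold 377 in 8 schools, the average would have to be 377/8 = 47.1 students per school.

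**5. Effect on power.** Same formula, with 44 x 0.70 = 30.8 analysed children per school and design effect 1 + 29.8 x 0.02 = 1.596.
- 16 schools: SE = sqrt(2 x 1.596/246.4) = 0.1138, 0.4/0.1138 = 3.51, 14 df, power 90%.
- 18 schools: 94%.
- 20 schools: 96%.

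The largest ICC that still gives 80% power for 0.4 SD is 0.039, 0.050 and 0.061 respectively. For the plan's base design of six full schools of 44 per group it is about 0.028.

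**The case against.** Four points can be made for the plan as written.

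*The extra schools may be meant for the whole trial.* Then 12 + 4 = 16. But the sentence says per group, and this reading still gives 352 places against 377 and still disagrees with the abstract.

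*The figure of 44 may mean participating children.* It is introduced as the school size behind the required 264, so this reading is open. Under Explanation for the choice of comparators (6b), whole classes play and only consented children are assessed, so the two counts do differ. If 44 are participants, 16 schools leave 8 x 44 x 0.8 = 282 per group after 20% loss, above 264. Likewise 264/0.8 = 330, and 330/44 = 7.5 gives 8 schools per group. This stands: a reader might infer that 16 schools can never deliver 264, but that holds only if 44 is eligible enrolment. It does not rescue the text, because the section states 377 and not 330 as the number to recruit, and the sentence still adds up to 20.

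*The 377 may look wrong.* A reader might object that the two rates should be applied in sequence, giving 264/0.72 = 367. Adding them is a slightly conservative convention, and 367/44 = 8.33 leads to the same 9 schools per group. There is no case for replacing 377.

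*Power is not threatened.* This also stands. After all the assumed losses, 16 schools have more power (90% against 85.8%) and tolerate a larger ICC (0.039 against about 0.028) than the base design the plan regards as sufficient.

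**Conclusion.** The inconsistency is real and shows on the face of the article: 16 is stated, 20 is what the sentence adds up to, and 18 is in the abstract. Taking 377 per group and an average of 44 per school as given, the count that fits is 9 per group and 18 in total, so both the number of extra schools and the total in the sample size section are wrong as written. At 44 per school, 16 schools are 25 places per group short of 377. The further shortfall against 264 (246 to 253 analysed) depends on 44 being eligible children before refusal, which the article does not say.

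A reader might infer that a trial with 16 schools would be underpowered. The document's own inputs do not support that: with 0.4 SD and ICC 0.02, power stays near 90%, because 264 was already rounded up to whole schools and two further clusters per group outweigh the missing children. What the count does change is the margin for error in the assumed ICC, from 0.039 with 16 schools to 0.061 with 20. This is therefore an incorrect sample-size figure that needs correction, with no loss of the stated power and no change to the analysis.

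**What to change.** Keep 377 per group. In Sample size {14}, replace the last sentence with one stating that three extra schools per group will be recruited, making 9 per group and 18 in total. If 16 or 20 schools is the true target, restate the students per school and the totals so that they agree with it; for example, 16 schools would need an average of about 47 to hold 377. State whether 44 counts eligible or participating children. Give the same school and student numbers in the abstract and the sample size section, and choose one of 750 or 754 as the student total.

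If 18 is the working target, this is a text correction only. If recruitment is being run to 16 or 20, the cost is a restated sample-size paragraph with matching totals.
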